### Chemotherapy and treatment sequencing

Platinum-based chemotherapy will be delivered by the medical oncologist according to local standards. Radiotherapy will usually start with cycle 2 of chemotherapy. However, at the discretion of the treating physician,radiotherapy may be started with cycle 1 (urgent cases), or after more than 2 cycles (e.g. where tumour downsizing is required). Concurrent chemotherapy cannot contain taxanes or gemcitabine.

### Follow-up and assessment of efficacy

#### Quality of life (QOL) and health utilities

QOL and health-utility data will be collected using the FACT-L scale and the EQ-5D, respectively.

The primary QOL endpoint will be based on the FACT-LCS (a subset of FACT-L) which measures pulmonary QOL specifically. As a secondary endpoint, the FACT-TOI incorporates the LCS with two additional domains from FACT-L: the Physical Well Being (PWB) and Functional Well-Being (FWB) scores. Although only subsets of FACT-L are used for these two endpoints, it is generally recommended that the full FACT-L be completed during clinical trials for more robust assessment of other QOL domains.

The EQ-5D measures health utility, and is used for calculating quality-adjusted survival and cost-utility.

#### Follow-up

Patients will be assessed by the radiation oncologist at 3 months, 6 months and 1 year, then every 6 months until two years, then annually until 5 years (Table 2). A detailed history, physical examinations and CT chest and upper abdomen will be performed with each assessment. Other investigations are as follows:

**Table 2 Tab2:** **Follow-up schedule**

	Before entry	Last week of radiotherapy	Month 3	Month 6	Bianually for 2 years then annually until year 5
History and Physical	X	X	X	X	X
Staging Imaging (see section 5)	X				
Pulmonary function tests and 6MWT at Robarts Research Institute	X		X		X
Baseline Bloodwork (see section 5)	X				
Pregnancy test for women of child-bearing age	X				
Toxicity and QOL Scoring (PAR, FACT-L, EQ-5D)	X	X	X	X	X (month 12 only)
Follow-up CT chest/upper abdomen			X	X	X

Toxicity scoring and QOL scoring (FACT-L and EQ-5D): during the last week of radiotherapy (i.e. at last patient review clinical visit), and at 3-, 6- and 12-months post-treatment.Pulmonary Function Tests and 6MWT: 3-months and 12-months post-treatment

### Statistics and sample size calculation

#### Sample size

The primary endpoint is the QOL score on the FACT-LCS measured 3-months post-treatment. A change in the LCS score of 2-3 points is considered clinically relevant [32]. Following concurrent CRT, it is assumed that in the arm receiving standard treatment, the mean post-treatment LCS score will be 20 [33]. The study will use a two-sided, independent-sample t-test with an alpha level of 0.05 and power of 80%, and will assume a 3-month QOL non-completion rate of 10%. The standard deviation of the LCS score is estimated to be 4. In order to detect a 3-point improvement in QOL in the experimental arm (Arm 2), a total of 64 patients will be required (32 in each arm).

#### Randomization

Randomization will occur in a 1:1 ratio between Arm 1 and Arm 2 using permuted blocks. Randomization results will be communicated by the statistician to the unblinded physicist by telephone.

#### Analysis plan

Patients will be analysed in the groups to which they are assigned (intention-to-treat). An independent-sample t-test will be used to compare QOL scores at 3-months. The percentage of patients in each arm who experience a clinically significant QOL decline (3 points) will also be reported. Survival will be calculated from date of randomization using the Kaplan-Meier method with differences compared using the log-rank test. A Cox multivariable regression analysis will be used to determine baseline factors predictive of survival. For the secondary endpoints involving QOL scales, linear mixed effects models will be used.

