## Background

### Radiation induced lung injury

Lung cancer is the most common cause of cancer death in men and women worldwide [1]. The large majority of lung cancer patients present with non-small cell lung cancer (NSCLC), and of these, approximately 30% present with locally advanced (stage III) disease. The current standard of care for locally advanced unresectable NSCLC is concurrent chemotherapy (CRT) with curative intent [2, 3]. Survival improvements of concurrent CRT over sequential CRT have been well-defined after multiple randomized trials, with concurrent CRT conferring a 10% overall survival benefit at two years [4, 5]; however, such treatment is associated with an increased risk of radiation-induced lung injury (RILI), including radiation pneumonitis (RP).

Clinically symptomatic RP occurs in 30-40% of patients after concurrent CRT and can have a major impact on quality of life, sometimes resulting in oxygen dependence, and in severe cases is fatal [6, 7]. Several factors are currently used to attempt to predict RP and to mitigate risk. Most of these predictive factors are metrics of the radiation dose delivered to normal lung, such as the volume of lung receiving ≥20 Gy of radiation, the mean lung dose and the dose per fraction of radiation. For example, a recent meta-analysis found that the volume of lung receiving at least 20 Gy (V20) is the best individual predictor of RP risk; a V20 > 40% is associated with a 35% risk of symptomatic RP, and >3% risk of fatal RP [7], supporting several previous single-institution studies [8] and a systematic review [6].

The risk of RP limits the radiotherapy dose that can be safely delivered. Although numerous modelling studies have indicated that higher doses of radiotherapy should be associated with improved oncologic outcomes, randomized data have shown that dose escalation leads to excess lung toxicity. The recent landmark RTOG 0617 randomized trial compared standard vs. high dose radiotherapy (60 Gy vs. 74 Gy), with concurrent chemotherapy, for locally advanced NSCLC. Overall survival at 18-months was 66.9% in the 60-Gy arm and 53.9% in the 74-Gy arm (p < 0.001), indicating inferior survival with dose-escalation [9].

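### The primary t-test compares surviving patients with a 3-month form, so intention-to-treat holds only as analysis by assigned arm; a baseline-adjusted repeated-measures model with a supportive rule for deaths would serve better

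*Protocol article*

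**What the plan says.** Under Sample size, the protocol article states: "The primary endpoint is the QOL score on the FACT-LCS measured 3-months post-treatment". The calculation is for a "two-sided, independent-sample t-test with an alpha level of 0.05 and power of 80" per cent, and it "will assume a 3-month QOL non-completion rate of 10" per cent. It takes a standard-arm mean of 20, a standard deviation of 4 and a 3-point improvement, and arrives at 64 patients, 32 per arm.

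Under Analysis plan: "Patients will be analysed in the groups to which they are assigned (intention-to-treat"). The primary method follows: "An independent-sample t-test will be used to compare QOL scores at 3-months". The percentage of patients in each arm with a 3-point decline is also to be reported; how a patient who dies enters that percentage is not stated. For the other scales and time-points the method differs: "For the secondary endpoints involving QOL scales, linear mixed effects models will be used".

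Table 2 (Follow-up schedule) has FACT-L, and so the LCS, collected before entry, in the last week of radiotherapy, and at months 3, 6 and 12.

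Under Interim analysis, the DSMC receives the 3-month completion rate and may recommend changing accrual to keep power.

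**The concern.** A two-sample t-test at one time-point uses only patients who have a score then. Anyone who has died, or is too ill to fill in the form, is outside the comparison unless a further rule brings them in, and the article gives none. The Background section explains why such loss is unlikely to be unrelated to outcome. It says that pneumonitis can lead to oxygen dependence and death, and that baseline quality of life predicted survival in the earlier dose-escalation trial. The patients lost may therefore include those whom functional avoidance is meant to protect.

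If loss of this kind differs by arm, the mean difference among completers is no longer the effect in the randomized groups. If the standard arm loses more of its sickest patients, a benefit is understated. If the avoidance arm loses more, a benefit is overstated or created. Adding patients, which is the interim remedy for low completion, restores power but does not remove this selection.

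The chosen test also makes no use of the baseline and end-of-radiotherapy LCS scores, although they are already collected and a mixed model is already planned for the secondary quality-of-life endpoints.

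**Working it through.** **1. Reproduce the sample size.** Inputs from Sample size: difference 3, SD 4, two-sided alpha 0.05, power 80%, non-completion 10%.

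- n per arm = 2 × (1.960 + 0.842)² × 4² / 3² = 27.9, rounded up to 28.
- 28 / 0.9 = 31.1, rounded up to 32 per arm, or 64 in total. This matches the plan.
- Expected completers: 32 × 0.9 = 28.8 per arm, about 58 in total. Power at that number is 0.81 (normal) or 0.80 (t).

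The arithmetic is sound. It also shows who is analysed: the design itself counts non-completers as lost from the primary test.

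**2. How much of the 10% could deaths use?** From the Background: "Overall survival at 18-months was 66.9% in the 60-Gy arm". This trial also prescribes 60 Gy, in 30 fractions. Assumptions: six weeks of radiotherapy (five fractions a week), so the 3-month form falls about 1.4 + 3 = 4.4 months after the start; and the other trial's survival applies here.

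- Constant hazard: −ln(0.669)/18 = 0.0223 per month; 1 − exp(−0.0223 × 4.4) = 9.4%.
- Hazard rising with time (Weibull shape 1.3 through the same 18-month point): 1 − exp(−0.402 × (4.4/18)^1.3) = 6.2%.
- Half the constant hazard: 4.8%.

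On these assumptions, deaths alone could use from about half to nearly all of the 10% allowance.

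**3. Effect of unequal loss.** Let non-completers score g points below completers on average, and let m be the fraction missing in an arm. The completer mean then exceeds the whole-arm mean by g × m. The shift in the contrast (avoidance minus standard) is g × (m_avoidance − m_standard). The article gives no value for g or for m by arm, so these are assumed.

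| g | Missing, standard v avoidance | Shift in contrast |
|---|---|---|
| 2 | 15% v 5% | −0.2 |
| 4 | 15% v 5% | −0.4 |
| 5 | 15% v 5% | −0.5 |
| 6 | 15% v 5% | −0.6 |
| any | 10% v 10% | 0 |

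Reversing the split reverses the sign.

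**4. Consequence for the test at g = 5.** Completers: 32 × 0.85 = 27.2 and 32 × 0.95 = 30.4. The standard error is 4 × √(1/27.2 + 1/30.4) = 1.056, with 55.6 degrees of freedom (noncentral t, SD among completers kept at 4).

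- No shift, true 3 points: noncentrality 3/1.056 = 2.84, power 0.797.
- Standard arm loses more: 3 appears as 2.5; noncentrality 2.37, power 0.643.
- Avoidance arm loses more, no true effect: spurious 0.5; noncentrality 0.47, two-sided rejection 0.075.

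**5. A different pattern.** Simulation with no true effect, removing the lowest-scoring 5 of 32 in the standard arm and 2 of 32 in the avoidance arm, gave a shift of about −0.6 points and a rejection rate of about 13%. The direction of the argument does not hang on one scenario, but the size does.

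**6. Price of ranking deaths worst.** Simulation with a true 3-point effect and non-completers ranked worst, missing at random in both arms:

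| Missing per arm | Completer t-test power | Worst-rank test power |
|---|---|---|
| 10% | about 0.81 | about 0.63 |
| 20% | about 0.75 | about 0.43 |

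This is why a worst-rank test suits a supportive rather than a primary role here.

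**The case against.** The strongest reply is that rules for deaths and missing forms belong in a statistical analysis plan, and a journal article need not carry them. That stands as far as missing detail goes: the article does not say in words that non-completers are dropped, and an analysis plan not shown here may add imputation or a rule for deaths. What remains is the method the article does fix: an unadjusted single-time-point test, sized on the footing that non-completers are lost.

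A second reply is that analysis by assigned arm is a legitimate meaning of intention-to-treat. It is, and the article defines the term that way. The point is only that the label says nothing about patients without a score.

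A third is that a mixed model is no cure, since it assumes data missing at random and implicitly carries scores past death. This also stands, and the fix allows for it.

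Several stronger readings are tempting but unsupported:

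- That at least 10% of forms will be missing. The 10% is a planning assumption, not a floor.
- That the primary and secondary estimates of 3-month LCS could conflict with no rule between them. The secondary LCS endpoint is defined at other time-points, and the t-test at 3 months is named as primary, so the order is fixed.
- That harm from avoidance would be hidden. Overall survival, provider-reported toxicity including pneumonitis, and semi-annual DSMC review with case review of grade 3-5 events would show severe harm, though outside the primary test.
- That low completion would go unaddressed. Power at 20% non-completion would be about 75%, but the interim check covers that loss of power.
- That a patient dying of pneumonitis is counted as not having declined. The article does not define the denominator, so this is inference.

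**Conclusion.** The concern holds in a limited form. As fixed in the article, the primary contrast is between surviving completers, and it leaves aside earlier LCS scores that could sharpen it and account for some missing forms. The sample size is correct.

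The bias is conditional. It is near zero if loss and its causes are balanced between arms, and can go either way if they are not. In the illustration it is 0.5 points, one-sixth of the 3-point target, with power of about 64% instead of about 80%, or a type I error of about 7.5% instead of 5%. Those figures rest on an assumed 15% v 5% split and an assumed 5-point deficit, neither of which comes from the article. The death estimate of 4.8% to 9.4% rests on another trial's 18-month survival and an assumed hazard shape. The change is worth making because the better analysis needs no new data; the documents do not show that the planned one must mislead.

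**What to change.** 1. Make the primary estimate the 3-month arm contrast from a mixed model for repeated LCS (last week of radiotherapy, months 3, 6 and 12), with arm, time and their interaction, adjusted for baseline LCS, in all randomized patients with any post-baseline form. This gains precision from baseline and handles missing forms that earlier scores explain among living patients.
2. Because that model assumes data missing at random and does not resolve death, prespecify one supportive rank analysis in which death before the 3-month form ranks worst. State that it is supportive because its power is lower.
3. Count death before 3 months as a decline in the 3-point decline percentage, and state the denominator.
4. Say that intention-to-treat here means analysis by assigned arm, and report the number randomized, dead, alive without a form, and analysed in each arm.

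The cost is analysis wording and a little programming. No extra visits, forms or patients are needed. The wording should be settled before outcome data are seen by arm.

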Toxicity outcomes from RTOG 0617, as scored by the health-care providers, did not initially appear to explain the inferior survival in the high-dose arm. Although there were more deaths due to radiation pneumonitis in the high-dose arm (5% vs. 1%) this did not meet statistical significance and only accounted for a small proportion of the overall survival difference between the two arms. However, *patient-reported outcomes* indicated a different toxicity profile; respiratory toxicity was common and was not often detected by the health-care providers. In the high-dose arm, 49% of patients exhibited a clinically-meaningful decline in the pulmonary quality of life (QOL) at 3-months, compared to 31% of patients in the low-dose arm (p = 0.024). Pulmonary QOL was also an important survival metric overall. Baseline QOL predicted for overall survival (OS) in multivariable analysis, more so than stage, performance status and other conventional prognostic factors [9].

In summary, for patients treated with standard concurrent CRT for locally advanced lung cancer, RP is a major source of morbidity, impairs quality of life, and can result in treatment-related death. RP also limits the dose of radiotherapy that can be safely delivered, and currently precludes radiotherapy dose escalation. RP is not well-ascertained by healthcare providers; in contrast, patient-reported QOL outcomes appear to be a powerful tool to capture pulmonary toxicity outcomes [9]. Clearly, better methods are needed to reduce pulmonary toxicity for patients undergoing concurrent CRT for lung cancer.

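### The primary t-test on the 3-month FACT-LCS is valid and powered as stated, but leaves out the scheduled baseline LCS and so gives up precision available at no cost

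*Protocol article*

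**What the plan says.** All places are in the protocol article.

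- **Endpoint (Sample size):** "The primary endpoint is the QOL score on the FACT-LCS measured 3-months post-treatment". This is a level at one time point, not a change from baseline.
- **Test (Sample size and Analysis plan):** the size is based on a "two-sided, independent-sample t-test with an alpha level of 0.05 and power of 80" per cent, and the Analysis plan repeats the choice: "An independent-sample t-test will be used to compare QOL scores at 3-months". Neither section names a covariate.
- **Planning values (Sample size):** "In order to detect a 3-point improvement in QOL in the experimental arm (Arm 2"), 64 patients are required, 32 per arm, with 10% not completing the 3-month form. "The standard deviation of the LCS score is estimated to be 4". Changes of 2 to 3 points are called clinically relevant.
- **Baseline measurement:** the row "Toxicity and QOL Scoring (PAR, FACT-L, EQ-5D") in Table 2 is marked before entry, and Study visits places QOL questionnaires at the pre-treatment visit. The section on quality of life and health utilities says that the LCS is part of FACT-L.
- **Other analyses (Analysis plan):** the percentage of patients with a 3-point decline is reported by arm, and linear mixed models are planned for the secondary QOL endpoints. No adjusted analysis of the primary endpoint is named.
- **Allocation (Randomization):** "Randomization will occur in a 1:1 ratio between Arm 1 and Arm 2 using permuted blocks". No stratification factor is named.

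**The concern.** Baseline and outcome are the same scale in the same patients, so some positive correlation is to be expected. A comparison that ignores the baseline leaves the variation it explains in the error term. In a trial of 64 patients sized at exactly 80% power, for the top of its own 2-to-3-point range, that precision is worth having.

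The second issue is chance imbalance. With about 29 analysed patients per arm and no stratification stated, the arms may differ at baseline, and part of that difference would appear in the unadjusted 3-month comparison. If adjustment is considered only after an imbalance has been seen, the choice is data-driven, so it should be fixed in advance.

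The primary test is stated in two sections. It is therefore a choice made in this document, not a detail left to an analysis plan.

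**Working it through.** **Inputs from the article:** difference 3 points, SD 4, two-sided alpha 0.05, power 80%, non-completion 10%, 32 patients per arm.

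**Inputs assumed:** r from 0.3 to 0.7, a baseline SD of 4 (equal to the stated LCS SD), and a baseline score for every patient with a 3-month score.

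**1. The plan's own figure.** Normal approximation: n per arm = 2 × 4² × (1.960 + 0.842)² / 3² = 27.9, rounded up to 28. Then 28 / 0.9 = 31.1, rounded up to 32 per arm, or 64 in total. The stated size reproduces. The exact noncentral-t calculation needs 29 completers per arm, which is close to the expected 32 × 0.9 = 28.8.

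**2. Power of the planned test.** With 28.8 per arm, SE = 4 × √(2/28.8) = 1.054 and the noncentrality is 3 / 1.054 = 2.85. Power by noncentral t is 80% for 3 points and 46% for 2 points.

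**3. Power with baseline adjustment.** Residual SD = 4 × √(1 − r²), with one further degree of freedom used. The equivalent gain in sample size is 1/(1 − r²) − 1.

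| r | Residual SD | Power, 3 points | Power, 2 points | Equivalent extra patients |
|---|---|---|---|---|
| none (t-test) | 4.00 | 80% | 46% | – |
| 0.3 | 3.82 | 83% | 50% | 1/0.91 − 1 = 10% |
| 0.5 | 3.46 | 90% | 58% | 1/0.75 − 1 = 33% |
| 0.7 | 2.86 | 97% | 74% | 1/0.51 − 1 = 96% |

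With 29 completers per arm instead of 28.8, power for 3 points is 80.1% unadjusted and 83.7%, 90.0% and 97.5% adjusted.

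**4. Chance baseline imbalance.** With 29 per arm, the SE of the baseline mean difference is 4 × √(2/29) = 1.05 points. The probability of a gap in either direction is 34% for 1 point or more and 5.7% for 2 points or more. With equal SDs at both times, the expected carry-over into the 3-month difference is r times the gap. For a 2-point gap this is 0.6 points (r = 0.3), 1.0 point (r = 0.5) or 1.4 points (r = 0.7), against a target effect of 3.

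**5. Would a change score do as well?** Its SD is 4 × √(2(1 − r)), which is 4.73 at r = 0.3 and 4.00 at r = 0.5. With 29 per arm, power for 3 points is 66% and 80% respectively. Below r = 0.5 it is worse than the planned t-test, so it is no substitute for ANCOVA.

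**The case against.** The strongest reply is that nothing here is wrong. The two sections name the same test, the sample size reproduces, and the t-test delivers its stated power. Randomization holds its type I error at 5%, and chance baseline imbalance is already part of its standard error. All of this stands. A reader might infer that the primary test is biased or that the trial is undersized, and the document supports neither. Imbalance distorts the result only conditionally on the gap that happens to occur.

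The size of the gain depends on a correlation that the article does not give. Baseline is taken before entry, radiotherapy takes 30 fractions and may follow more than two chemotherapy cycles, and the outcome comes 3 months after treatment. A low r cannot be excluded, and at r = 0.3 the gain is only about 3 percentage points of power. This also stands: the direction is secure, the amount is not.

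Three further readings are tempting but go beyond the text:

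- **That a baseline gap passes in full into the result.** Only a fraction r of it does, on average.
- **That the article shows baseline LCS to be prognostic for this endpoint.** The Background sentence, "Baseline QOL predicted for overall survival (OS) in multivariable analysis", concerns survival in another trial. It is context and does not inform r.
- **That the trial is known to be unstratified with complete baseline data.** The article names no strata, but the full protocol may. The baseline form is scheduled, which does not guarantee completion.

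The article also has safeguards. At the interim analysis the committee checks the SD and completion rate and may recommend a change in accrual, and mixed models are planned for the secondary QOL endpoints. Neither adjusts the primary test. Finally, the trial was sized for 3 points, so the 2-point power figures describe the design and are not a shortfall against its stated aim.

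**Conclusion.** The point holds as a free improvement to the primary analysis. The planned t-test is valid and has 80% power for 3 points with 64 patients. Adjusting for baseline LCS would raise that to between 83% and 97% for r between 0.3 and 0.7. It would also remove the expected carry-over of 0.6 to 1.4 points should a 2-point baseline gap arise, an event with a probability of about 6%.

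The figures rest on the article's SD of 4 and 10% non-completion. They also rest on an assumed baseline SD of 4, an assumed range for r, and baseline scores being available for the patients analysed. The recommendation does not depend on the exact r: even at 0.3 the gain exceeds the cost of the one degree of freedom.

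**What to change.** In the Analysis plan, replace the t-test as primary analysis by ANCOVA of the 3-month LCS on treatment arm with baseline LCS as covariate. Report the adjusted mean difference with its 95% CI as the primary result, and keep the unadjusted t-test as a supportive analysis. In Sample size, keep 64 patients and state that this number was calculated for the unadjusted test, so that any gain from adjustment serves as a reserve of power.

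The cost is a sentence in each of the two sections and one degree of freedom. No additional patients, visits or questionnaires are needed, although completion of the baseline form now matters for the primary analysis. The change should be made before outcome data by arm are seen, which includes the QOL data that the data safety monitoring committee receives by arm at the interim analysis.

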## Methods/design

### Objectives

#### General objective

To determine if functional lung avoidance based on ^3^He MRI improves quality of life outcomes for patients with NSCLC undergoing concurrent CRT.

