#### Secondary endpoints

Pulmonary QOL at other time-points

○ Measured using the FACT-LCS

Other QOL scores

○ FACT—Trial Outcomes Index (FACT-TOI)

○ FACT—Lung (FACT-L) and subscales

Provider-reported toxicity (including RP and esophagitis)

○ Assessed by the National Cancer Institute Common Toxicity Criteria (NCI-CTC) version 4

Overall Survival

○ Defined as time from randomization to death from any cause

Progression-free survival

○ Time from randomization to disease progression at any site or death

○ Progression defined according to RECIST 1.1

Quality-Adjusted Survival (based on EQ-5D)

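### The plan's only survival regression is aimed at prognostic factors, which no listed objective asks about; aiming it at the randomized arm would be a minor but nearly free improvement

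*Protocol article*

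**What the plan says.** The Analysis plan in the protocol article deals with survival in two sentences. The first is the comparison of the arms: "Survival will be calculated from date of randomization using the Kaplan-Meier method with differences compared using the log-rank test". The second gives the regression model its purpose: "A Cox multivariable regression analysis will be used to determine baseline factors predictive of survival".

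The questions the trial sets itself are listed under Objectives. The General objective asks whether functional lung avoidance "improves quality of life outcomes for patients with NSCLC undergoing concurrent CRT". Under Secondary endpoints, OS is "Defined as time from randomization to death from any cause" and PFS is "Time from randomization to disease progression at any site or death". None of these entries asks which baseline factors predict survival.

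The nearest link is in the Background, where an earlier dose-comparison trial is reported: "Baseline QOL predicted for overall survival (OS) in multivariable analysis, more so than stage, performance status and other conventional prognostic factors".

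**The concern.** The arms are randomized and OS and PFS are endpoints of that comparison, so the natural use of a survival model is to estimate the arm effect. The article's stated use is a prognostic question outside its own objectives. The Background already names the likely predictors: baseline QOL, stage and performance status. All three are recorded before treatment. The Follow-up schedule table has FACT-L before entry, and stage and ECOG status are inclusion criteria. They are therefore available as adjustment covariates.

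Two things are at stake. First, a log-rank p-value alone does not show how large a survival difference the data leave open. That matters when a QOL gain is weighed against tumour control, because Planning workflow and blinding relaxes the homogeneity and conformity constraints for avoidance plans only. Second, an unadjusted comparison gives up some power if the named factors are truly prognostic.

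**Working it through.** **The plan's own figure.** The sample size comes from the QOL endpoint: difference 3, SD 4, two-sided alpha 0.05, power 80%, 10% non-completion. n per arm = 2 × (1.96 + 0.84)² × 4² / 3² = 27.9, so 28. Then 28 / 0.9 = 31.1, so 32 per arm and 64 in total. The stated 64 is reproduced. The article gives no figure for the survival analysis, so the rest rests on assumptions.

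**Expected deaths.** The only survival rate at this dose in the article is 66.9% at 18 months, in the 60 Gy arm of the earlier trial (Background). Assume a constant hazard, the same in both arms, and no censoring before the time point.

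- Hazard = −ln(0.669) / 1.5 = 0.268 per year.
- Deaths by 2.5 years = 64 × (1 − e^(−0.268 × 2.5)) = 31.
- Deaths by 5 years = 64 × (1 − e^(−0.268 × 5)) = 47.

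**Precision of the arm hazard ratio.** With 1:1 allocation the standard error of the log hazard ratio is about 2/√deaths. With 47 deaths the 95% factor is exp(1.96 × 2/√47) = 1.77, so an estimate near 1 has an interval of about 0.57 to 1.77. With 27 deaths (about 2 years) it is about 0.47 to 2.14.

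**Power, unadjusted against adjusted.** Simulation with 64 patients, 5-year follow-up, a true OS hazard ratio of 0.5 and one prognostic score of assumed strength. At this hazard ratio fewer deaths occur: 32 × (1 − e^(−1.34)) + 32 × (1 − e^(−0.67)) = 23.6 + 15.6, about 39. The ranges cover repeat simulations.

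| Log HR per SD of the score | Unadjusted | Adjusted Cox | Gain (points) |
|---|---|---|---|
| 0.3 | 52–53% | 54–56% | about 2–4 |
| 0.5 | 50–51% | 56–57% | about 5–7 |
| 0.7 | 43% | 55–57% | about 12–14 |

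With 1,500 trials per cell, the simulation error of one percentage near 50% is √(0.25/1500) = 1.3 points. The gain in the first row is therefore barely distinguishable from none. A smaller run of 500 trials per cell (error about 2.2 points) gave gains of 5, 7 and 16 points. The adjusted model's type I error was about 5–6%. With covariates that are not prognostic, it lost about 2 points of power.

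**Room for covariates.** Arm plus three covariates is four terms: 47/4 = 11.8 deaths per term at 5 years and 31/4 = 7.8 at 2.5 years. That supports two or three covariates, not a long list.

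**Chance findings if factors are read off the model.** If no factor matters and each is tested at 0.05, simulated Cox models with N = 64 declare at least one factor predictive in about 14–18% of trials with 3 factors, 26% with 5 and 50% with 10. The article does not give the number of factors, so only the range can be stated.

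**The case against.** The strongest reply is that nothing here is wrong. Comparing randomized groups "using the Kaplan-Meier method with differences compared using the log-rank test" is standard for secondary endpoints. The article states an intention-to-treat analysis and names no stratification factors under Randomization, so an unstratified test fits the design. The Kaplan-Meier curves also show survival by arm. All of this stands.

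A reader might infer three stronger things that the text does not support:

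- **That arm is left out of the Cox model, or that no hazard ratio will be reported.** The article states neither. A covariate list, a selection rule and the reporting of a hazard ratio are commonly left to the full protocol or SAP, and their absence from an article is no finding.
- **That a stepwise search is planned which will yield a false factor half the time.** No selection procedure is described, and the 50% figure needs ten null factors. With three it is about 14–18%, and the three named in the Background have prior support.
- **That survival is unprotected.** Both plans carry the same prescription and target-coverage requirement, neither may be clearly superior in target coverage, and the DSMC sees OS by arm at the interim analysis.

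Two technical limits also stand. Adjustment barely narrows the interval, so the fix displays the imprecision rather than curing it. The simulated unadjusted hazard ratio of 0.51 to 0.55 against a conditional 0.50 reflects a different estimand, not a faulty test. A true hazard ratio of 0.5 is also a very large effect for a trial sized on QOL.

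What remains is the mismatch on the page: the stated aim of the only survival regression answers no listed question.

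**Conclusion.** The point holds as a minor improvement to the analysis of secondary endpoints. The log-rank test is not an error. The stated purpose of the Cox model matches no objective or endpoint, and the same model aimed at the arm would serve the trial better.

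The power gain is about 2 to 13 points at 5 years, assuming constant hazard from the earlier trial's 60 Gy arm, complete follow-up, a true OS hazard ratio of 0.5 and prognostic strength of 0.3 to 0.7 log hazard ratio per SD. It is close to nil at the weak end and turns into a loss of about 2 points if the covariates are uninformative. The steadier benefit is that the interval of about ×/÷ 1.77 would be in view, so that a non-significant test is not taken as evidence of equal survival.

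That the log-rank sentence also covers PFS is an inference, since the Analysis plan speaks only of survival.

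**What to change.** Replace the Cox sentence with wording such as: OS and PFS will each be analysed with a Cox model containing randomized arm and two or three covariates fixed before unblinding (baseline FACT-LCS, stage IIIA versus IIIB, ECOG status); the arm hazard ratio with its 95% confidence interval will be reported, alongside Kaplan-Meier curves and the log-rank test. Add that any reading of the covariates as prognostic factors is exploratory.

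Keeping the log-rank test leaves the interim OS stopping rule as it is. Naming both endpoints settles how PFS is analysed.

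The cost is one or two sentences and no new data. The covariates must be few and chosen in advance because deaths are few, and the small power loss with uninformative covariates has to be accepted.
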